### 3.3.7 Blinding of Investigational Medicinal Product

Given that the products have quite different physical properties, it is not possible to blind treating clinicians to group assignment. To minimize bias, treating clinicians will be blinded to group assignment until immediately prior to IMP infusion. The blood bank technologist will randomize the patient to PCC or FP, according to the randomization schedule, and prepare and release the product in a tamper sealed container (with weight device in PCC boxes to ensure adequate concealment). The operating room personnel will be blinded to group allocation until the tamper lock seal is broken in the operating room immediately prior to infusion. For the second order, a tamper-sealed container will not be used and the blood bank technologist will release IMP as determined by the randomization schedule, as per usual practice. The type of IMP administered will not be recorded in the chart to ensure that the research personnel assessing outcomes and AEs are blinded to assignment. Patients will also be blinded to treatment allocation.

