**Study Procedures:**

When the first order for PCC or FP is received by the blood bank, the technologist will confirm patient eligibility with the clinical team. Following confirmation of eligibility, the technologist will randomize the patient to PCC or FP according to the randomization schedule and prepare and release the product in a tamper sealed container (with weight device in PCC boxes to ensure adequate concealment). The operating room personnel will be blinded to group allocation until the tamper lock seal is broken in the operating room immediately prior to infusion. The rate and route of administration of products will be documented according to current standards.

If a second order is received within 24 hours of randomization, the blood bank technologist will release IMP as determined by the randomization schedule, as per usual practice (a tamper-sealed container will not be used for the second order). For subsequent orders in the operating room and intensive care unit (ICU), the technologist will release FP for both groups.

The type of IMP administered will not be recorded in the chart to ensure that the research personnel assessing outcomes and AEs are blinded to assignment. Patients will also be blinded to treatment allocation.

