### 3.3.8 Drop-outs and Crossovers

**Drop-outs:** We anticipate that <20% of randomized patients will either not receive the treatment, will not have undergone an index cardiac procedure, or will not consent to remain in the study. The majority will likely be the first reason, in whom coagulation factor replacement will be deemed to be not necessary after it was ordered but before it is administered due to cessation of bleeding or identification of other causes of bleeding. Study sample size has been calculated to compensate for drop-outs.

**Product switching:** Other than the coagulation factor replacement order being cancelled, all patients will be treated according to the randomization schedule on the first and second times when coagulation factor replacement is ordered for the treatment period (24 hours after randomization). Following this, all patients will receive FP when coagulation factor replacement is ordered. To ensure minimal product switching, instructions will be entered into the blood bank information system to dictate the randomization product for the 24 hours after randomization and will flag the laboratory technologists if attempts are made to override the instruction.

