### **4.4 Assignment of Patients to Treatment Groups**

Patients will be assigned to treatment with either PCC or FP using a permuted-block, stratified (by centre) random allocation scheme prepared by a biostatistician not involved in the conduct of the trial. Group allocation will apply to the first two doses of IMP during the treatment period (up to 24 hours from randomization). For any additional doses (i.e., the third dose and thereafter), patients in both groups will receive FP. Subjects/patients are not permitted to re-enroll in the study.

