### 3.4 Intention-To-Treat (ITT) Population

The Intention-To-Treat (ITT) population will include all enrolled patients who have given informed consent and who received at least one treatment with either PCC or FP and underwent cardiac surgery. In the event that a patient receives treatment that is not in concordance with the randomization schedule, the treatment group will be defined according to the randomization (rather than the actual treatment received).

|                           |                 |             |               |
|---------------------------|-----------------|-------------|---------------|
| Statistical Analysis Plan | Version 2.0     |             | Page 10 of 19 |
| Sponsor                   | [name] | Protocol No | FARES         |

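### The tamper seal follows the first order rather than the first infusion, so a patient re-ordered after a cancelled first order could get the first actual dose unsealed

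*Combined protocol and SAP*

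**What the plan says.** **Sealing.** Section 3.3.7 describes the first release: "The operating room personnel will be blinded to group allocation until the tamper lock seal is broken in the operating room immediately prior to infusion". It then says of the next release: "For the second order, a tamper-sealed container will not be used". The synopsis, under Study Procedures, agrees: "a tamper-sealed container will not be used for the second order". Section 5.2 gives the purpose of the boxes as preserving the blind until the product is infused, and does not limit this to the first order.

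**Cancellation.** Section 3.3.8 expects fewer than 20% of randomised patients to be lost for three reasons together: no treatment, no index procedure, or no consent. The first is expected to dominate and concerns patients "in whom coagulation factor replacement will be deemed to be not necessary after it was ordered but before it is administered". The same section keeps the allocation instruction in the blood bank system for 24 hours from randomisation.

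**Number of randomised releases.** Section 3.3.8 counts orders: "all patients will be treated according to the randomization schedule on the first and second times when coagulation factor replacement is ordered", with cancellation named as an exception. The synopsis (Study Procedures) also counts orders, and after the second it says: "For subsequent orders in the operating room and intensive care unit (ICU), the technologist will release FP for both groups". Section 4.4 counts doses: "Group allocation will apply to the first two doses of IMP during the treatment period".

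**Analysis set.** SAP section 3.4 limits the ITT population to consenting patients "who received at least one treatment with either PCC or FP and underwent cardiac surgery". Protocol section 9.2 likewise excludes randomised patients who received no IMP.

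**The concern.** The products look different, and section 3.3.7 accepts that clinicians cannot be blinded once the product is in hand. The sealed box is therefore the only described safeguard that keeps the decision to infuse or cancel independent of the arm. That decision matters here because the ITT population is conditional on treatment. A patient who is randomised but not infused leaves the primary analysis.

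For a first order that is used, the safeguard works. For a patient whose first order is cancelled and who later needs coagulation factor, the next release is by number the second order and goes out unsealed. The team then sees the product before deciding whether to give it. If that decision differs by product, the ITT groups differ by more than chance. The SAP would not show it, because the SAF population (3.3) and even the All Patients Enrolled population (3.1) also require at least one treatment.

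The second issue is what is released next. After one cancelled order and one infused dose, counting orders and counting doses give different products in the PCC arm.

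**Working it through.** **1. One patient's path under the literal wording.**

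| Step | Seal (3.3.7, synopsis) | Product if orders are counted (synopsis Study Procedures, 3.3.8) | Product if doses are counted (4.4) |
|---|---|---|---|
| First order, cancelled unused | sealed | randomised product, not given | randomised product, not given |
| Second order, first actual dose | not sealed | randomised product | randomised product |
| Third order, second actual dose | not sealed | FP in both arms | randomised product |

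The seal gap is in the second row and does not depend on how releases are counted. The conflict over product is in the third row and arises only if the patient is cancelled, re-ordered and infused, and then ordered again within 24 hours.

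**2. How consistent the order and dose wording is.**
- Orders only: synopsis Study Procedures; 3.3.8.
- Doses for the allocation or for the switch to FP: synopsis dose section; 4.4; section 6.
- Both in the same text: synopsis Study Design; 3.2; 3.3.2; 5.1.1 (dosing schedule); SAP 1.2. Most of these tie the allocation to the first and second times an order is placed, 3.3.2 to each order, and all put the switch to FP at the third dose.

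The wordings agree as long as no order is cancelled, and diverge once one is.

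**3. Size.** The plan gives no figure for this event. The nearest is the allowance from 120 randomised to 100 evaluable. It implies a loss of 1 − 100/120 = 16.7%, within the stated ceiling of under 20% (a full 20% would leave 120 × 0.80 = 96). Neither figure counts the patients at issue: someone cancelled, re-ordered and then infused is treated and is not a drop-out.

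An illustration therefore needs two assumed shares: *c*, the share of first orders cancelled unused, and *r*, the share of those re-ordered within 24 hours.

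Number affected = 120 × *c* × *r*

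| | *r* = 5% | *r* = 25% | *r* = 50% |
|---|---|---|---|
| *c* = 5% | 0.3 | 1.5 | 3.0 |
| *c* = 10% | 0.6 | 3.0 | 6.0 |
| *c* = 20% | 1.2 | 6.0 | 12.0 |

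The middle case is 120 × 0.10 × 0.25 = 3 patients, or 2.5% of those randomised.

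**The case against.** The strongest reply is that the unsealed second order simply means the order for the second dose. Several sections (the synopsis dose section, 3.3.2, 5.1.1 and section 6) describe the second release as an order for a second dose, and the protocol uses the two words loosely throughout. Sections 3.3.7 and 5.2 state the aim as blinding until infusion, and 3.3.8 sets cancelled orders apart. On that reading a re-ordered patient would still get a sealed box.

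The reply adds that re-ordering is an inference. Section 3.3.8 describes cancelled patients as no longer needing the product and treats them as drop-outs, and 4.3.1 lets the investigator withdraw a patient whose bleeding has stopped. Concealment of the allocation up to randomisation is intact. Patients and outcome assessors stay blinded. The study is a pilot with no statistical sample size.

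Much of this stands, and it sets the priority. It does not close the gap. The two places that describe the seal both count orders, and a technologist following them would send a re-order unsealed. Section 4.3.1 grants a right to withdraw rather than a duty, and the 24-hour instruction remains active.

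A reader might go further and infer that a cancelled order uses up one of the two randomised releases, so that such patients in the PCC arm are moved to FP after a single dose. The documents do not support this as settled: section 4.4 and the repeated third-dose wording say otherwise. Any extra plasma would also be only partly felt in P2, because SAP 4.6 repeats the total blood product analysis without FP.

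**Conclusion.** The point holds in a limited form. The sealing rule as written does not carry out the protocol's own aim when a first order is cancelled and the patient is re-ordered. This opens a route by which entry to the ITT population could depend on the arm. Nothing in the documents shows that it would happen often, or that clinicians would act on it.

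The number affected is unknown and probably small: about 0.3 to 12 of 120 over the assumed shares, and 3 in the middle case. A reader might derive as many as 16 by treating all losses at the 20% ceiling (24 patients) as cancelled and never re-ordered, with 40% of cancelled orders re-ordered. That would need 24/0.6 = 40 cancelled first orders, a third of all patients. It would also read a ceiling over three reasons as a count of one. It is not supportable.

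On the number of randomised releases, the finding is a conflict between order-based and dose-based text, with no established loss of a release. It could reach the per-protocol set. FP given at the third order after one PCC dose complies under one reading. Under the other it may be a product different from the one assigned, which is a default exclusion in SAP 3.5.

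This is a cheap improvement of minor priority. Its main value is that the Phase 3 trial this pilot is meant to inform should not inherit the gap.

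**What to change.** 1. In section 3.3.7 and the synopsis (Study Procedures), consistent with 5.2, state that every release goes out in a tamper-sealed container until the patient's first IMP infusion has started.
2. Record whether the seal on each returned box is intact. If it was broken before cancellation, the arm is already known and resealing later releases restores nothing, so this record identifies those patients.
3. Reconcile the order-based text (synopsis Study Procedures; 3.3.8) with the dose-based text (synopsis dose section; 4.4; section 6) and the mixed text (synopsis Study Design; 3.2; 3.3.2; 5.1.1; SAP 1.2), so that all say how an order cancelled unused is counted. Which count is right is for the sponsor and investigators; this review takes no position.
4. Optionally, flag in the analysis data any patient whose first IMP came from a re-order and report the number by arm. A separate run of the primary endpoints without so few patients, chosen on an event after randomisation, would add little.

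The cost is a few extra sealed boxes, one sentence in the blood bank procedure and one data field. No extra patients are needed.

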**Packaging and Labeling**

Commercial supplies of *Octaplex* will be used. Several batches of IMP may be used throughout the study. The batch numbers will be recorded in the CRFs and reported in the final study report.

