## 6 STUDY CONDUCT

All patients having cardiac surgery with or without CPB at the study centres will be the potential patients in the study. Patients will be randomized if they bleed or are thought to have a high potential to bleed (see section 4.1.1) after the start of surgery and the clinical team determines that coagulation factor replacement is required according to current clinical standards for up to 24 hours after randomization. Once the clinical team orders coagulation factor replacement, the blood bank technologist will confirm patient eligibility and randomize the patient (according to a prepared randomization schedule) to *Octaplex* or FP and prepare the product.

For 24 hours from randomization, patients may receive 1500 IU *Octaplex* for IBW $\leq$ 60 kg or 2000 IU *Octaplex* for IBW $>$ 60 kg, or 3 U FP for IBW $\leq$ 60 kg or 4 U FP for IBW $>$ 60 kg, as per randomized group allocation. If an order for a second dose is received, the second dose of *Octaplex* or FP will be released and administered to patients according to the randomized group allocation as per the first dose. For any additional doses (i.e., the third dose and thereafter), patients in both groups will receive FP (in 1 U increments at the discretion of the ordering physician).

Standard coagulation measures, including INR, EXTEM CT and MCF, and fibrinogen level, will be obtained as per usual clinical practice ideally within 75 minutes before and after each IMP administration. Due to the nature of bleeding in these cases, however, IMP doses can be administered before these results are obtained or the test results are released by the laboratory. Clinical indications for IMP administration are bleeding in the setting of suspected or confirmed low coagulation factor levels, as indicated by EXTEM CT  $>90$  seconds, which is the treatment threshold recommended by the validated and standardized TACS algorithm (see Figure 2; next page) (4), or INR  $>1.5$ . In certain circumstances, such as uncontrolled bleeding, clinicians may deem it necessary to administer coagulation factor replacement in cases where EXTEM CT is  $<90$  seconds (or INR is  $<1.5$  if ROTEM not being used).

All AEs and SAEs occurring until POD-28 will be recorded. Patients will be followed by research coordinators in each institution. All clinical outcomes will be obtained from patients' medical records and electronic records, history and physical where needed, and via phone contact during the follow-up visits.

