### 6.1.2 Visit 1: First post-randomization visit (0 to 24 hours after randomization)

For any specified activity that cannot be completed on this visit, additional visits will be made until all study data are obtained.

- Obtain consent from patient or surrogate
- Collect baseline data
  - Demographics
  - Medical history
  - Preoperative concomitant medications
- Collect surgical data
  - Intraoperative concomitant medications
  - CPB start and end times
  - Cross-clamp time
  - Circulatory arrest start and end times
  - Fluid in- and output monitoring
  - Inotropes and vasopressors
- Collect laboratory assessments where available as part of routine care
  - Chemistry (sodium, potassium, chloride, bicarbonate, pH)

- Hematology (complete blood count)
  - Coagulation profile before and after IMP administration
  - Safety labs (creatinine, liver function tests [ALT, ALP], bilirubin, troponin)
- Collect all transfusion and hemostatic agents (number and timing) for the 24 hour period after randomization
- Collect bleeding components using the e-CABG and UDPB criteria (1, 72) as well as a modified version of the UDPB not including PCC and FP requirements
- Collect extubation time
- Collect concomitant medications
- Collect AEs and SAEs

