##### Collection of AEs

The condition of the patient will be monitored throughout the study. At each visit, whether scheduled or unscheduled, AEs will be elicited using a standard non-leading question such as “How have you been since the last visit/during the previous study period?” In addition, the research assistant will check the patient records for any documented event.

Any AE or ADR which occurs during the study will be noted in detail on the appropriate pages of the CRF. If the patient reports several signs or symptoms representing a single syndrome or diagnosis, the diagnosis should be recorded in the CRF. The Investigator will grade the severity of all AEs or ADRs (mild, moderate, or severe), the seriousness (non-serious or serious), and the likelihood that they were related to the IMP (causality). The Sponsor will be responsible for assessing the expectedness of each ADR (expected or unexpected).

Diseases, signs and symptoms, and/or laboratory abnormalities already present before the first administration of IMP will not be considered AEs unless an exacerbation in intensity or frequency (worsening) occurs.

The Investigator will provide detailed information about any abnormalities and about the nature of and reasons for any action taken as well as any other observations or comments that may be useful for the interpretation and understanding of an AE or ADR.

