### **Causality of AEs**

All AEs will be assessed by a blinded Investigator as to whether they can be explained by the patient's underlying condition or surgical course. If they are not explainable, then the Investigator will make a determination of the relationship of the AE with the IMP as follows:

**Probable:** reports including good reasons and sufficient documentation to assume a causal relationship, in the sense of plausible, conceivable, likely, but not necessarily highly probable. A reaction that follows a reasonable temporal sequence from administration of the IMP; or that follows a known or expected response pattern to the suspected medicine; or that is confirmed by stopping or reducing the dosage of the medicine and that could not reasonably be explained by known characteristics of the patient's clinical state.

**Possible:** reports containing sufficient information to accept the possibility of a causal relationship, in the sense of not impossible and not unlikely, although the connection is uncertain or doubtful, for example because of missing data or insufficient evidence. A reaction that follows a reasonable temporal sequence from administration of the IMP; that follows a known or expected response pattern to the suspected medicine; but that could readily have been produced by a number of other factors.

**Unlikely:** reports not following a reasonable temporal sequence from IMP administration. An event which may have been produced by the patient's clinical state or by environmental factors or other therapies administered.

**Not related (unrelated):** events for which sufficient information exists to conclude that the etiology is unrelated to the IMP.

**Unclassified:** reports which for one reason or another are not yet assessable, e.g., because of outstanding information (can only be a temporary assessment).

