#### **8.1.2 Case Report Forms**

Authorized study site staff (e.g., blood bank technologist, research coordinator/assistant) will be responsible for completing an eCRF record for each patient enrolled. All site personnel will be trained on completion of a patient's eCRF. The site is also provided with the approved eCRF Completion Guidelines which will assist in data entry and data issues/questions. Additional site training may be provided as refreshers throughout the study, if needed. All persons allowed to enter or to change eCRF data must be listed in the Delegation of Authority Log.

For each patient enrolled, an eCRF record will be completed within the EDC system and finally approved by the Investigator or an authorized sub-investigator.

Prior to operational use, the eCRF application will be validated. All site personnel will be trained on the EDC system and study specific eCRFs prior to receiving access to the live system for data entry.

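### The plan calls its outcome and adverse-event assessors blinded, but its one stated safeguard leaves other routes to product identity open

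*Combined protocol and SAP*

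**What the plan says.** Protocol 5.2 describes a partially blinded study in which patients and outcome assessors do not know the allocation and treating clinicians do. The mechanism for assessors, given in 3.3.7 and repeated in 5.2 and the synopsis, is: "The type of IMP administered will not be recorded in the chart", which is done "to ensure that the research personnel assessing outcomes and AEs are blinded to assignment". The sealed box serves a different purpose: it conceals the product from operating room staff until infusion. For harms, 7.4.2 (Causality of AEs) adds: "All AEs will be assessed by a blinded Investigator". Section 5.2 also says that breaking the blind is not an issue in this study.

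Other sections set out who handles the data:

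- Section 6: "Patients will be followed by research coordinators in each institution".
- Section 6.1.2 (Visit 1): "Collect all transfusion and hemostatic agents (number and timing) for the 24 hour period after randomization". The same list includes the e-CABG and UDPB components and the AEs and SAEs.
- Section 5.1.1 (Packaging and Labeling), on Octaplex: "The batch numbers will be recorded in the CRFs".
- Section 7.4.2 (Collection of AEs): "The Investigator will grade the severity of all AEs or ADRs". The same sentence gives the Investigator seriousness and causality.
- Section 8.1.2: each eCRF record is "finally approved by the Investigator or an authorized sub-investigator". Section 8.1.3 has the Investigator approve all eCRFs before database lock.

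**The concern.** Leaving the product out of the chart protects an assessor only if the chart is the assessor's only source. Here it is not.

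This matters because the protocol's background (1.1) gives readers product-specific expectations: TRALI and TACO with plasma, and a possible excess of thrombosis and kidney injury with PCC. An assessor who knows the product may look for such events, or attribute them, differently by arm. Section 3.1.2 says transfusion reactions at imputability of possible or higher will be compared. SAP 4.7.1 tabulates events by relationship and by worst severity within each treatment group. Detecting early safety issues is a stated use of the pilot (1.2). If these judgements were made with the product known, the report would still call them blinded.

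**Working it through.** The documents give no figure on this point, so there is none to reproduce. The check sets the blinding claim against each route by which product identity can reach an assessor.

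1. **Visit 1 tasks (6.1.2).** One undivided list covers transfusions and hemostatic agents with timing, UDPB components, and AEs/SAEs. UDPB Table 4 (7.2.3) has columns for FP units and for PCC. The modified score was created because the standard score contains both. Whoever completes the standard score sees the product.
2. **Source of transfusion data (7.2.2).** It is the blood bank databases, so a restriction on the chart does not hide it.
3. **Endpoint S1 (SAP 4.6).** It counts PCC and FP doses, so product identity must be in the study data.
4. **Batch numbers (5.1.1).** They are recorded in the CRFs under the Octaplex heading. A completed Octaplex batch field points to PCC.
5. **Source rule (8.1.1).** All eCRF data must be supported by the patient records. This pulls against keeping the product out of the chart, unless blood bank records are treated as a separate source. The plan does not say so.
6. **Approval (8.1.2, 8.1.3).** The Investigator grades AEs and also approves eCRFs. No order between the two steps is stated.
7. **Definitions.** The causality categories in 7.4.2 refer to the known response pattern of the suspected medicine. ISBT imputability relates the event to what was transfused. Both are hard to apply without the product, and the plan does not say what information the grader has.

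Against these routes, the plan requires no separate unblinded collector, no restricted eCRF view, and no locking of AE grading before product data become visible.

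**Illustration only.** The recording probabilities and true rates below are assumptions. Only the 50 evaluable patients per arm comes from the documents (9.1).

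- Observed rate = true rate × probability of being recorded or attributed.
- Example: 0.10 × 0.90 = 9.0% and 0.10 × 0.70 = 7.0%. Risk ratio = 9.0/7.0 = 1.29.
- 95% half-width for the difference = 1.96 × √(0.09 × 0.91/50 + 0.07 × 0.93/50) = 10.6 points.

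| True rate, both arms | Recorded, arm A v B | Observed | Risk ratio | Difference (points) | 95% half-width (points) |
|---|---|---|---|---|---|
| 10% | 90% v 80% | 9% v 8% | 1.125 | 1 | 10.9 |
| 10% | 90% v 70% | 9% v 7% | 1.29 | 2 | 10.6 |
| 10% | 80% v 50% | 8% v 5% | 1.60 | 3 | 9.6 |
| 20% | 90% v 80% | 18% v 16% | 1.125 | 2 | 14.7 |
| 20% | 90% v 70% | 18% v 14% | 1.29 | 4 | 14.3 |
| 20% | 80% v 50% | 16% v 10% | 1.60 | 6 | 13.1 |

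In patients, 9% v 7% of 50 is 4.5 v 3.5, a difference of one. A distortion of this kind could move a point estimate and could not be told apart from chance at this sample size.

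**The case against.** The strongest reply is that nothing here proves anyone is unblinded. The Visit 1 list names no actor. Section 8.1.2 names the blood bank technologist, who must know the product, among those who may complete the eCRF, and it lets a sub-investigator approve the record. Approval may come after grading, so approval alone need not unblind the grader. The eCRF layout, delegation log, completion guidelines and site procedures are not in the documents and might provide the separation. Plasma use alone is also an imperfect marker, because both arms receive FP from the third dose.

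All of this stands, and it limits the point. A reader might infer that the assessors are in fact unblinded, or that every AE judgement is exposed. The documents support neither. They permit separation; what they lack is any requirement for it.

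Two further inferences should also be resisted:

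- **TACO.** The figure of about 5% in 1.1 is per transfusion and is given for FP. It cannot serve as a per-patient rate in both arms.
- **Kidney injury.** The expectation about PCC is mixed. Section 1.1 cites studies that found an association, and also a pooled odds ratio of 0.80 (95% CI 0.58 to 1.12).

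It is also fair to say that this is a pilot with descriptive safety analysis. That limits the consequence but does not make the label accurate.

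**Conclusion.** The concern holds in this form: the stated safeguard does not secure the stated blinding when the plan is followed as written. This goes beyond missing detail, because the plan's own procedures carry product identity to places the safeguard does not reach.

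Most exposed are judged items: causality, severity, and TRALI/TACO imputability. Least exposed are death and events defined by laboratory values. Thromboembolic events are grouped by MedDRA queries once recorded, although recording them still depends on staff.

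The conclusion is that attribution can differ by arm, not that it does. Neither the direction nor the size can be derived from the documents. The risk ratio of 1.29 rests wholly on the assumed 90% and 70% and only shows scale. Reading the task list as shared work, and the eCRF as revealing the product, are inferences from the text. The change should be made: it costs little, and this pilot informs the Phase 3 design.

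**What to change.** 1. Have the blood bank technologist enter IMP type, batch, dose and PCC/FP units, including the PCC and FP components of UDPB, on separate eCRF forms.
2. Hide those forms from the coordinator and the grading Investigator until severity, seriousness and causality are locked. Have a different authorised sub-investigator approve them.
3. Assign ISBT imputability as a documented second step, after the clinical diagnosis has been recorded. State who assigns it and with what information.
4. Leave total fluid balance visible, because it bears on the recognition of circulatory overload. Keep emergency access to the product identity for patient care.
5. Reconcile the blinding statements in 3.3.7, 5.2 and 7.4.2 with 5.1.1 (batch numbers), 6.1.2, 7.2.2 and 8.1.1 to 8.1.3. Split the Visit 1 list by role, and name blood bank records as the source for product data.

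If this is not done, remove the word blinded, as applied to assessors, from 3.3.7, 5.2 and 7.4.2, and report the AE assessment as not reliably blinded.

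The cost is EDC permission settings, protocol wording and a slightly more complex set-up and sign-off, using existing staff. Treatment and sample size do not change. Imputability would still be judged with the product known, so that item should be reported as such.
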